#### **Week 1 $\pm 2$ days after first injection**

The following should be performed in the intratympanic injection arm and combination treatment arm:

- Pure tone audiogram (0.5-8.0kHz range)
- 2nd intratympanic injection

NOTE: complete resolution of hearing may allow intratympanic steroid treatment to be terminated after only one treatment

#### **Week 2 $\pm 2$ days after first injection**

The following should be performed in the intratympanic injection arm and combination treatment arm:

- Pure tone audiogram (0.5-8.0kHz range)
- 3rd intratympanic injection

NOTE: complete resolution of hearing may allow intratympanic steroid treatment to be terminated after only two treatments

#### **Week 6 $\pm 7$ days after randomisation**

The following should be performed and/or collected:

- Pure tone audiogram (0.5-8.0kHz range)
- AB phoneme speech testing
- Participant complete questionnaires to include SSQ, VRBQ, TFI, HUI3, ICECAP-A
- AE/SAE monitoring
- Compliance reporting
- Resource usage

#### **Week 12 $\pm 7$ days after randomisation**

The following should be performed and/or collected:

- Pure tone audiogram (0.5-8.0kHz range)
- AB phoneme speech testing
- Participant complete questionnaires to include SSQ, VRBQ, TFI, HUI3, ICECAP-A.
- Resource usage
- AE monitoring (intratympanic injection arm and combination treatment arm only for persistent perforation of the tympanic membrane)

For participants who have internet access and agree to use the online digits-in-noise and pure tone tests, they will be asked to perform the tests on the trial website every week, for 12 weeks from randomisation. In rare cases where the hearing tests are unable to be performed due to an infection in either ear, the infection should be treated as per standard local protocols and the audiogram performed as soon as the infection has cleared.

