## **7.7 Intervention modification or cessation**

As specified in section 7.3, complete resolution of hearing may allow intratympanic steroid treatment to be terminated after only one or two treatments. A rare complication of intratympanic injection is further hearing loss. Where this is observed on pure tone audiometry, no further treatments will be given. In the rare event that a study participant chooses to change treatment type or has a significant side effect from oral steroids and is advised to modify or stop the treatment by their treating clinician this will be recorded. On rare occasions, changes to the intervention schedule may be required based on participant request or adverse events. The allocated interventions may be discontinued if a participant requests to cease treatment or cross over to another arm. Adverse events such as allergic reaction, or a change in patient status, such as development of poor blood glucose control may alter the risk-benefit profile for that individual and the treating clinician should discuss this with the patient and alter the provided intervention, if required. Details of treatment

---

adherence, treatment modifications or treatment discontinuation at the Investigator's discretion should be documented in the source data.

Any modification of the interventions, or cross over to another trial arm will also be recorded on the CRFs.

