| Resource usage                                         |           |          |                                               |                                               |                    | All               | All                  |
| Adverse Events monitoring                              |           |          |                                               |                                               |                    | All               | 2,3 & |
| Compliance reporting                                   |           |          |                                               |                                               |                    | All               |                      |
| Oral steroid provision                                 |           | 1,3      |                                               |                                               |                    |                   |                      |
| Intratympanic injection                                |           | 2,3      | 2,3                                           | 2,3                                           |                    |                   |                      |

---

1 = for arm 1 (oral steroid), 2 = for arm 2 (intratympanic injection), 3 = for arm 3 (combined treatment)

#Optional, for participants who have internet access.

\* should be performed within three days prior to commencement of treatment

\*\*recommended to be performed on same day as pure tone audiogram or if not practicable within next working day

& Only persistent perforation of the tympanic membrane will be recorded at 12 weeks

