## 10.3 Adverse Event reporting in STARFISH

The safety profile for this trial population and interventions are well characterised so a strategy of targeted reporting of AEs will not affect the safety of participants.

Only the following AEs will be reported on the 6 week follow up CRF:

- 
- Further sudden deterioration of hearing after intervention
  - Affective disorders
  - Psychotic reactions
  - Stomach ulcer
  - Acute ear infection (otitis externa or media)
  - New dizziness onset or worsening after intervention
  - New tinnitus onset or worsening after intervention
  - Persistent ear drum perforation at 6 week review
  - Allergic reaction to steroid preparation
  - Allergic reaction to local anaesthetic

Only the following AEs will be reported on the 12 week follow up CRF:

- Persistent perforation of the tympanic membrane

The reporting period for AEs will be from commencement of trial treatment until the 12 week follow up visit (see above for further details of timeline requirements of AE reporting).

The reporting period for Serious Adverse Events (SAEs) will be from commencement of trial treatment until 6 weeks post treatment commencement. All AEs which meet the SAE definition should be reported as per section 10.4.

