## 11.2 Case Report Form Completion

CRFs should be completed for each individual participant.

The CRFs will include, but not be limited to, the forms listed in Table 9.

**Table 9:** List of trial specific CRFs

| Form Name                    | Schedule for submission                                                                                                                                                      |
|------------------------------|------------------------------------------------------------------------------------------------------------------------------------------------------------------------------|
| Screening log                | When a patient presents with ISSNHL and is considered for approach to participate in the STARFISH trial                                                                      |
| Contact details form         | Following consent                                                                                                                                                            |
| Randomisation CRF            | At the point of randomisation                                                                                                                                                |
| Clinic visit form            | At baseline (i.e. following consent and randomisation);
At 2nd injection visit (if applicable);
At 3rd injection visit (if applicable);
At 6 weeks;
At 12 weeks. |
| Participant-complete booklet | At baseline (i.e. following consent and randomisation);
At 6 weeks;
At 12 weeks.                                                                                       |

|                                  |                                                                        |
|----------------------------------|------------------------------------------------------------------------|
| Serious Adverse Event Form       | In accordance with section 10                                          |
| Trial Exit/Change of status Form | At the point of becoming aware of withdrawal/change of status or death |

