## 14.2 Analysis of outcomes

A separate Statistical Analysis Plan (SAP) will be produced and will provide a more comprehensive description of the planned statistical analyses. The reporting of the outcomes will be based on the guidelines as published in the Reporting of multi-arm parallel-group randomised trials (22). A brief outline of these analyses is given below.

The objective of the trial is to test the superiority of three interventions:

- Oral steroid
- Intratympanic steroid
- Combination oral and intratympanic steroid

All analysis will have the following two key group comparisons:

- Intratympanic steroid versus oral steroid
- Combination oral and intratympanic steroid versus oral steroid

Oral steroid group will be considered as the control group, i.e. reference category for all analyses. A comparison of intratympanic steroid versus combination oral and intratympanic steroid will also be performed as part of an exploratory analysis for all outcomes.

All primary analyses (primary and secondary outcomes including safety outcomes) will be by intention-to-treat (ITT), i.e. all participants will be analysed in the intervention group to which they were randomised irrespective of adherence to randomised intervention or other protocol deviation. As a secondary (or sensitivity) analysis, a per-protocol analysis will also be carried out for the primary outcome.

To maintain an overall 5% type I error rate, each comparison will be tested at a significance level of 2.5% to account for the increase in the risk of type I error associated with making two key comparisons. Therefore, for the primary outcome and all other secondary outcomes measures, a Bonferroni correction (23) will be applied to account for the increase in the risk of type I error associated with making two key comparisons (i.e. “intratympanic steroid versus oral steroid” and “combination oral and intratympanic steroid versus oral steroid”).

For all outcome measures, appropriate summary statistics and differences between groups, e.g. mean differences, relative risks, absolute differences will be presented, with two-sided 97.5% confidence intervals. Outcomes will be adjusted for the minimisation variables listed in section 6.4.3 and any baseline values (where applicable).

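### Section 9 and Table 3 schedule the week-12 perforation entry for the two injection arms only, while 10.3 sets no arm limit; read by allocation, an oral-arm participant who crosses over to injection has no scheduled week-12 entry for this harm

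*Protocol*

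**What the plan says.** Five parts of the Protocol bear on who has a perforation recorded at week 12.

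- **Section 9, Week 12** lists "AE monitoring (intratympanic injection arm and combination treatment arm only for persistent perforation of the tympanic membrane". The restriction is by arm.
- **Table 3** agrees. The adverse-event row covers all arms at week 6 and arms 2 and 3 at week 12. The codes are defined in the table notes as the trial arms, and the week-12 footnote reads "Only persistent perforation of the tympanic membrane will be recorded at 12 weeks".
- **Section 10.3** introduces its second list with "Only the following AEs will be reported on the 12 week follow up CRF". The only item is persistent perforation, and no arm is named. Its 6-week list includes "Persistent ear drum perforation at 6 week review", also with no arm named.
- **Section 8.2.2** lists adverse events relevant to the interventions as an outcome recorded at 6 and 12 weeks, without an arm limit. **Table 9** (section 11.2) lists one "Clinic visit form" at 12 weeks for everyone.
- **Section 7.7** states that "The allocated interventions may be discontinued if a participant requests to cease treatment or cross over to another arm" and that "Any modification of the interventions, or cross over to another trial arm will also be recorded on the CRFs". It describes a change of treatment type as rare.

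On analysis, section 14.2 puts safety outcomes under intention-to-treat and adds: "Oral steroid group will be considered as the control group, i.e. reference category for all analyses".

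**The concern.** Perforation of the eardrum is a harm of the injection, so it should be looked for in whoever was injected. Section 9 and Table 3 instead tie the week-12 entry to the arm. Allocated arm and treatment received can differ, because 7.7 allows crossover. Section 7.11.1 also foresees it, since adherence in the oral arm requires that no intratympanic treatment was given.

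The texts leave sites with two possible instructions. A site working from section 9 or Table 3 would leave the item blank in the oral arm. A site working from 10.3 might complete it for everyone. A blank oral-arm item at week 12 could then mean that no perforation was found or that the question was not asked. Since oral is the reference category, the week-12 item would have no planned record in the arm against which the other two are compared.

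**Working it through.** The Protocol states no figure on this point, so the check is a comparison of texts, followed by a bound on who is affected.

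**1. Coverage by visit and arm**

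| Item | Week 6 | Week 12 |
|---|---|---|
| Otoscopy (Table 3) | all arms | all arms |
| Adverse-event monitoring (Table 3) | all arms | arms 2 and 3 |
| Perforation item (10.3) | no arm limit | no arm limit |
| Clinic visit form (Table 9) | no arm limit | no arm limit |

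The week-12 adverse-event cell is the only one that is narrower than its neighbours. The examination that would reveal a perforation is planned for all; the entry that would report it is not.

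**2. Who falls in the gap.** Anyone allocated to arm 2 or 3 has the week-12 entry, whatever treatment they received. Oral-arm participants who stay on oral treatment have no injection and so no injection harm to report. That leaves only oral-arm participants who cross over to injection.

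**3. What can be lost for them.**
- A perforation present at the week-6 review is captured, because that item covers all arms.
- Whether that perforation is still there at week 12 has no scheduled entry.
- A perforation caused by an injection after the week-6 review has no scheduled entry. On the protocol's own injection timetable the third injection falls about two weeks after the first, so this needs a late crossover.

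**4. How many people.** Section 14.1 gives 175 per arm and 157 per arm after 10% attrition. The Protocol gives no crossover share *b*, so it has to be assumed. Participants without the scheduled entry = 157 × *b*:
- *b* = 1%: 157 × 0.01 = 1.57
- *b* = 5%: 157 × 0.05 = 7.85

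These are counts of participants without a scheduled entry, not of perforations. The information lost is smaller still: only the participants among them who fall under the second or third item in step 3. The Protocol gives no perforation or persistence rate, so no expected count of lost events is offered.

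**The case against.** The strongest reply is that the texts can be read together. Section 10.3 says which events go on each form; section 9 and Table 3 say who is monitored at each visit. The 6-week list in 10.3 includes allergy to local anaesthetic, which belongs to the injection procedure, and it too names no arm. Silence there need not mean every arm. This stands in part: the conflict is a soft one, but the documents do not state which reading a site should take.

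A second reply is that arm may mean the pathway a participant is on. Section 7.7 uses the word for the treatment crossed over to, and Table 3 codes the injection visits themselves as arms 2 and 3, so a site might apply the whole injection pathway, including the week-12 check, to a crossover participant. Allocation is the more natural reading of the codes, but it is not stated. If both readings are open, the text needs the correction anyway.

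A third reply is that targeted reporting is a deliberate choice in 10.3, and that oral prednisolone cannot perforate an eardrum. That justifies leaving out oral-arm participants who were never injected. It does not justify leaving out those who were.

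A reader might go further and infer that an oral-arm perforation would go wholly unseen at week 12. The documents do not support that. Otoscopy is scheduled for all arms, section 6.5 has an ENT team member examine the ear before outcome audiometry, and section 10.2 describes recording adverse events in the notes as routine. The case report form is not shown, so it may hold an otoscopy field, and a missing item might be recovered by a data query.

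**Conclusion.** The point holds as a minor inconsistency in data collection. Read by allocation, section 9 and Table 3 give an injected oral-arm participant no scheduled week-12 adverse-event entry for perforation, and 10.3 does not clearly settle the matter. The size is very small: crossover is described as rare, week 6 already captures perforations in every arm, and only persistence to week 12 or a perforation from a late injection is at risk. The conclusion rests on reading the arm codes as allocation and on at least some oral-to-injection crossover. The 1% and 5% shares are illustrations, since the Protocol gives no rate.

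Three stronger inferences should be resisted. The intention-to-treat safety comparison is sound and is not in question. Participants who enter with a dry perforation, which 4.2 allows, are not missed events: the condition predates treatment, adverse-event reporting runs from the start of treatment, and baseline otoscopy covers all arms. And nothing here touches the primary outcome, the sample size or any trial conclusion.

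**What to change.** In section 9 (Week 12), replace the arm restriction with wording such as: 'AE monitoring, all arms, for persistent perforation of the tympanic membrane, recorded from the scheduled otoscopy'. In Table 3, change the week-12 adverse-event entry from arms 2 and 3 to all arms. State in 10.3 that the 12-week item applies to all arms.

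If the sponsor prefers to keep the item targeted, the minimum change is to require it for every participant who received an intratympanic injection, whatever the allocated arm, and to say so in section 9, Table 3 and 10.3 alike.

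The cost is a line in section 9, one table cell and a phrase in 10.3. The visit, otoscopy and clinic form are already planned, and crossover is already recorded. The downside of the all-arm version is one extra yes/no item for up to 175 oral-arm participants, nearly all of whom can be expected to have no perforation. The intention-to-treat safety analysis stays as it is.

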**Table 3: Schedule of Assessments**

| Assessments                                            | Visits    |          |                                               |                                               |                    |                   |                      |
|--------------------------------------------------------|-----------|----------|-----------------------------------------------|-----------------------------------------------|--------------------|-------------------|----------------------|
|                                                        | Screening | Baseline | From first injection                          |                                               | From randomisation |                   |                      |
|                                                        |           |          | 2 nd injection
(week 1 ±2 days) | 3 rd injection
(week 2 ±2 days) | Weekly             | Week 6
±7 days | Week 12
±7 days   |
| Eligibility check                                      | All       |          |                                               |                                               |                    |                   |                      |
| Valid informed consent                                 |           | All      |                                               |                                               |                    |                   |                      |
| Relevant medical history taken                         |           | All      |                                               |                                               |                    |                   |                      |
| Concomitant medication check                           |           | All      |                                               |                                               |                    |                   |                      |
| Demographic information                                |           | All      |                                               |                                               |                    |                   |                      |
| Randomisation                                          |           | All      |                                               |                                               |                    |                   |                      |
| Otoscopy                                               |           | All      | 2,3                                           | 2,3                                           |                    | All               | All                  |
| Pure tone audiogram (0.5-8.0kHz range)                 |           | All*     | 2,3                                           | 2,3                                           |                    | All               | All                  |
| AB phoneme speech testing                              |           | All**    |                                               |                                               |                    | All               | All                  |
| Online digits-in-noise test #               |           |          |                                               |                                               | All #   |                   |                      |
| Online pure tone audiogram test #           |           |          |                                               |                                               | All #   |                   |                      |
| Speech, Spatial and Qualities of hear scale (SSQ)      |           | All      |                                               |                                               |                    | All               | All                  |
| Vestibular Rehabilitation Benefit Questionnaire (VRBQ) |           | All      |                                               |                                               |                    | All               | All                  |
| Tinnitus Functional Index (TFI)                        |           | All      |                                               |                                               |                    | All               | All                  |
| Health Utilities Index 3 (HUI3)                        |           | All      |                                               |                                               |                    | All               | All                  |
| ICECAP-A                                               |           | All      |                                               |                                               |                    | All               | All                  |
| Resource usage                                         |           |          |                                               |                                               |                    | All               | All                  |
| Adverse Events monitoring                              |           |          |                                               |                                               |                    | All               | 2,3 & |
| Compliance reporting                                   |           |          |                                               |                                               |                    | All               |                      |
| Oral steroid provision                                 |           | 1,3      |                                               |                                               |                    |                   |                      |
| Intratympanic injection                                |           | 2,3      | 2,3                                           | 2,3                                           |                    |                   |                      |

---

1 = for arm 1 (oral steroid), 2 = for arm 2 (intratympanic injection), 3 = for arm 3 (combined treatment)

#Optional, for participants who have internet access.

\* should be performed within three days prior to commencement of treatment

\*\*recommended to be performed on same day as pure tone audiogram or if not practicable within next working day

& Only persistent perforation of the tympanic membrane will be recorded at 12 weeks

